**Adapted version of the Strengths and Difficulties Questionnaire (SDQ) impact supplement (Goodman, 1999)**

| Overall, do you think that you have difficulties around eating, food, body shape and/or body weight? | No | Yes – minor difficulties | Yes – definite difficulties | Yes – severe difficulties |
| --- | --- | --- | --- | --- |

If you have answered “Yes”, please answer the following questions about these difficulties:

| How long have these difficulties been present? | Less than a month | 1-5 months | 6-12 months | Over a year |
| --- | --- | --- | --- | --- |

| Do the difficulties upset or distress you? | Not at all | Only a little | Quite a lot | A great deal |
| --- | --- | --- | --- | --- |

| Do the difficulties interfere with your everyday life in the following areas? | Not at all | Only a little | Quite a lot | A great deal |
| --- | --- | --- | --- | --- |
| Home life |  |  |  |  |
| Friendships |  |  |  |  |
| Classroom learning |  |  |  |  |
| Leisure activities |  |  |  |  |

| Do the difficulties make it harder for those around you (family, friends, teachers, etc.)? | Not at all | Only a little | Quite a lot | A great deal |
| --- | --- | --- | --- | --- |

**Additional question regarding self-harm and suicidality**

| Are you currently having thoughts about hurting yourself or ending your life? | Yes/No |
| --- | --- |

About your health

| 1. | Do you have an eating disorder diagnosis? | Yes/No |
| --- | --- | --- |
|  | *If yes to 1 – please specify:* |  |
|  | *Which eating disorder you have* | Avoidant/Restrictive Food Intake Disorder (ARFID)  Anorexia Nervosa  Bulimia Nervosa  Binge Eating Disorder  Other Specified Feeding or Eating Disorder (OSFED) |
|  | *How old were you when you were diagnosed with an eating disorder* |  |
|  | *Who diagnosed you with an eating disorder (e.g., CAMHS, private treatment provider)* |  |
| 2. | Are you currently receiving any psychological treatment for your eating disorder (e.g., family-based therapy, cognitive behavioural therapy, counselling etc.)? | Yes/No |
|  | *If yes to 3 – please specify:* |  |
|  | *What treatment you are currently receiving (e.g., family based therapy, cognitive behavioural therapy, counselling etc.)* |  |
|  | *The length and duration of the treatment (i.e., the number of sessions you have received/will receive in total)* |  |
|  | *When you are due to finish this treatment (if known)* |  |
|  | *Where you are receiving this treatment (e.g., CAMHS, private treatment provider)* |  |
| 3. | Are you currently prescribed any medication for mental health difficulties (e.g., sertraline, fluoxetine)? | Yes/No |
|  | *If yes to 3 – please specify:* |  |
|  | *What medication you have been prescribed* |  |
|  | *How long you have been taking this medication at the current dosage* |  |
| 4. | Are you currently on the waitlist for treatment for an eating disorder? | Yes/No |
|  | *If yes to 4 – please specify:* |  |
|  | *What treatment you are waiting to receive (e.g., CBT, counselling, medication, not known)* |  |
|  | *Where you are waiting for treatment (e.g., CAMHS, private treatment provider)* |  |
| 5. | Have you previously received treatment for an eating disorder? | Yes/No |
|  | *If yes to 5 – please specify:* |  |
|  | *What treatment you received (e.g., family based therapy, cognitive behavioural therapy, counselling etc.)* |  |
|  | *The length and duration of the treatment (i.e., if a psychological therapy, the number of sessions you received and over what time period or if medication, what medication and for how long were you taking this medication)* |  |
|  | *How old you were when you received this treatment* |  |
|  | *Where you received this treatment (e.g., CAMHS, private treatment provider)* |  |
| 6. | Have you received a diagnosis for any other mental health condition? | Yes/No |
|  | *If yes to 6 – please specify*  What other mental health condition(s) you have |  |

Other

| Is there any other information that you think is relevant that we haven’t asked? |  |
| --- | --- |

**Appendix 1c. Initial Screening Questionnaire for CYP under 16**

About you

| Your name: |  |
| --- | --- |
| Your parent/carer’s name: |  |
| Your parent/carer’s phone number: |  |
| Your parent/carer’s email address: |  |

About your difficulties

The following questions will help us to understand if you may have difficulties around eating which may get in the way of doing things.

**Child Eating Disorder Examination Questionnaire (ChEDE-Q8; Kliem et al., 2017)**

| These questions are about the past two weeks only (14 days).  Please read each question carefully and circle the response for each question. | | Scoring | | | | | | |
| --- | --- | --- | --- | --- | --- | --- | --- | --- |
| On how many days of the past 14 days… | | No days | 1-2 days | 3-6 days | 7 days | 8-10 days | 12-13 days | Every day |
| Restraint over eating | …have you been trying to cut down on food to control your weight or shape? |  |  |  |  |  |  |  |
| Food avoidance | …have you tried not to eat any foods you like to control your weight and shape? |  |  |  |  |  |  |  |
| Preoccupation with food | …has thinking about food or calories made it much harder to concentrate on things you are interested  in; for example, reading, watching tv, or doing your homework? |  |  |  |  |  |  |  |
| Feelings of fatness | …have you felt fat? |  |  |  |  |  |  |  |
| Desire to lose weight | …have you had a very strong wish to lose weight? |  |  |  |  |  |  |  |
| Guilt about eating | Over the past 2 weeks/14 days: How often have you felt guilty after eating because of the effect on your shape and weight?  (Do not count binges – times when you have eaten a really big amount of food and felt out of control) |  |  |  |  |  |  |  |
| Dissatisfaction with weight | Over the past 2 weeks/14 days: How unhappy have you felt about your weight? |  |  |  |  |  |  |  |
| Discomfort seeing body | Over the past 2 weeks/14 days How uncomfortable have you felt seeing your body: for  example, in the mirror, in shop windows, when you undress  or when you have a bath or shower? |  |  |  |  |  |  |  |

**Adapted version of the Strengths and Difficulties Questionnaire (SDQ) impact supplement (Goodman, 1999)**

| Overall, do you think that you have difficulties around eating, food, body shape and/or body weight? | No | Yes – minor difficulties | Yes – definite difficulties | Yes – severe difficulties |
| --- | --- | --- | --- | --- |

If you have answered “Yes”, please answer the following questions about these difficulties:

| How long have these difficulties been present? | Less than a month | 1-5 months | 6-12 months | Over a year |
| --- | --- | --- | --- | --- |

| Do the difficulties upset or distress you? | Not at all | Only a little | Quite a lot | A great deal |
| --- | --- | --- | --- | --- |

| Do the difficulties interfere with your everyday life in the following areas? | Not at all | Only a little | Quite a lot | A great deal |
| --- | --- | --- | --- | --- |
| Home life |  |  |  |  |
| Friendships |  |  |  |  |
| Classroom learning |  |  |  |  |
| Leisure activities |  |  |  |  |

| Do the difficulties make it harder for those around you (family, friends, teachers, etc.)? | Not at all | Only a little | Quite a lot | A great deal |
| --- | --- | --- | --- | --- |

**Additional question regarding self-harm and suicidality**

| Are you currently having thoughts about hurting yourself or ending your life? | Yes/No |
| --- | --- |

**Appendix 2. Additional demographic questionnaire for parents/carers at baseline**

About you

| Caregiver status: | Primary caregiver  Secondary caregiver  Shared caregiver  Other |
| --- | --- |
| Relationship status: | Single, never married or civil partnered  Living with partner  Married or civil partnered  Divorced  Separated  Widowed  Not applicable |
| Highest level of education: | School completion  Further education (e.g., college, vocational courses)  Higher education (undergraduate degree)  Postgraduate qualification |
| Employment status: | Unemployed  Employed full-time  Employed part-time  Retired  Student |
| *If employed, please state occupation:* |  |

About you and your health

| 1. | Do you have personal lived experience of an eating disorder? | Yes/No |
| --- | --- | --- |
|  | *If yes to 1 – Have you sought help for this?* | Yes/No |
| 2. | Do you have personal lived experience of another mental health condition? | Yes/No |
|  | *If yes to 2 – Have you sought help for this?* | Yes/No |

**Appendix 3. Treatment acceptability questionnaire (adapted from Creswell et al., 2010)**

|  |  | Strongly disagree | Disagree | Neither agree or disagree | Agree | Strongly agree |
| --- | --- | --- | --- | --- | --- | --- |
| 1. | Overall, I am satisfied with the treatment I received |  |  |  |  |  |
| 2. | I am satisfied with the programme I received |  |  |  |  |  |
| 3. | I am satisfied with the support I received from the guide |  |  |  |  |  |
| 4. | I am satisfied with the number of support sessions I received |  |  |  |  |  |
| 5. | I am satisfied with the length of the support sessions I received |  |  |  |  |  |
| 6. | I am satisfied with the outcomes of the treatment I received |  |  |  |  |  |
| 7. | I would recommend this treatment approach to other families |  |  |  |  |  |

| 8. What aspects of this treatment did you like the most? |
| --- |
|  |

| 9. What aspects of this treatment did you like the least? |
| --- |
|  |

| 10. How can we improve this treatment for families in the future? |
| --- |
|  |

| 11. Please provide any other feedback or comments |
| --- |
|  |

*Adapted from: Creswell, C., Hentges, F., Parkinson, M., Sheffield, P., Willetts, L., & Cooper, P. (2010). Feasibility of guided cognitive behaviour therapy (CBT) self‐help for childhood anxiety disorders in primary care. Mental Health in Family Medicine, 7(1), 49–57.*

**Appendix 4. Indicative Topic Guide – Qualitative post-intervention feedback interview**

*Please note that the questions below are examples of the types of questions that children, young people and parents/carers might be asked post-intervention (with the wording of the questions being modified accordingly). The interview will be semi-structured and by nature, flexible in response to individual needs.*

Aim: To explore CYP, and parents/carers, experiences of the guided self-help intervention, with a particular focus on acceptability

1. **Introduction**

Establish the purpose of the interview and the limits of confidentiality

1. **Contextual information**

Review relevant contextual information with CYP or parent/carer. For example:

- Age of child
- Diagnoses
- Number of support sessions received
- Who attended the support sessions

1. **Initial views of the treatment approach (e.g., when they first heard about the study, read the participant information sheet and/or spoke to the study researcher)**

- What were your initial views of this treatment?
- What were your initial thoughts on the possible benefits/challenges of this approach?
- What were your views on how the study information was presented?
- Was there anything that you found particularly helpful/unhelpful at this stage?
- Was there anything else you would have liked at this stage?

1. **Experiences of receiving the treatment**

- Did your views of the treatment approach change once you started treatment?
- What did you like/dislike about the treatment approach?
- Probe for benefits for the CYP/parent/family
- Probe for challenges for the CYP/parent/family
- How did you/your child find implementing the treatment techniques at home?
- How did you/your child respond to this approach?

1. **Relevance of treatment to family**

- Do you feel that the treatment has had any positive/negative impact on the difficulties it was aimed at helping with?
- Explore what the particular difficulties being targeted
- Probe what has improved for the CYP
- Probe what has not improved for the CYP
- Do you think the issues covered in the treatment were relevant to the family?
- Probe what issues were relevant and why
- Probe what issues were not relevant and why

1. **Experiences of the mode, content and structure of the treatment (programme and sessions)**

- How did you/your child find the treatment programme?
- Probe for views on content, style, length
- Probe for any suggestions of things they would have found helpful/preferred to receive
- How did you/your child find completing the module activities?
- Explore understanding of tasks
- Probe for views on content, style, length
- Probe for any suggestions of things they would have found helpful/preferred to receive
- How did you/your child find the support sessions?
- Probe for views on content, frequency, duration, rapport
- Probe for whether they felt sufficiently supported to implement the strategies from the programme
- Probe for any suggestions of things they would have found helpful/preferred to receive

1. **Broader acceptability of the approach**

- Would you recommend this approach to other families?
- Probe for reasons why/why not
- Were there any issues that were not covered in the treatment that you wish were covered?
- Probe what would have been helpful to cover
- Probe what impact they think covering these issues would have had
- What would you change about this approach?
- What would you have liked more/less of with this approach?
- Do you have any suggestions for improvement to the treatment?
- How have you found continuing to implement the techniques now the sessions have ended?

1. **Summarise the interview**

Probe whether there is anything else that the CYP or parent wishes to add or comment on. Thank the person for their time.

**Appendix 5. Risk and Safeguarding Management Protocol**

1. **Introduction**

The guidelines outlined here apply to the management of risk and safeguarding issues that arise in the context of work carried out with families for this research project. All risk and safeguarding issues will be managed in accordance with relevant national polices and guidelines (see section 3).

1. **Research Activities**

The study researchers will engage in activities where potential risk and/or safeguarding issues may arise. These include:

- Unstructured telephone contacts with participants or potential participants (e.g., explaining study procedures, arranging appointments)
- Structured telephone and/or videocall contacts to conduct questionnaires and/or qualitative interviews with participants
- Written information received from participants or potential participants (e.g., emails, completed questionnaires)
- Guidance sessions conducted with participants

## Definition of risk and safeguarding

Risk refers to (i) risk to self; (ii) risk to others; (iii) risk from others; (iv) neglect to self, and (v); neglect from others. Safeguarding refers to the welfare of an individual and/or ensuring individuals are protected from harm. The study researchers have a responsibility to respond to risk and/or safeguarding information. Risk and/or safeguarding information may be in relation to the study participants (e.g., child, young person, parent) and/or someone else.

## Procedures for managing risk and/or safeguarding concerns

The procedures for managing risk and/or safeguarding concerns are outlined below.

## *4.1. Unstructured contact with participants and/or potential participants (e.g., to explain study procedures, to arrange appointments)*

Whenever the study researchers have an unstructured contact with a participant or potential participant, there is a chance that this person may disclose risk and/or safeguarding information.

The study researchers will have access to support from the study supervisors ([name] and [name], who are both Clinical Psychologists) when making unstructured contact with families, in the event risk and/or safeguarding information arises, and action needs to be taken. The study researchers will only make unstructured contacts with participants or potential participants between the hours of 8am and 8pm Monday to Friday so that one of the study supervisors will be available to contact via email and/or their mobile phones if needed.

In the event that a risk and/or safeguarding concern arises during unstructured contacts with participants or potential participants, the study researchers will:

1. Thank the individual for sharing the information and find an early opportunity to explain that this information may need to be shared with the study supervisors and, if necessary, other relevant professionals (e.g., their GP, their eating disorder clinician). Note – an eating disorder clinician will only be contacted if the family remain on the eating disorder service’s caseload during their time within the study (i.e., when on waitlist for assessment/treatment), and if the study supervisors identify that an eating disorder clinician needs to be informed. The eating disorder clinician can then record this information on their electronic patient record system
2. Explain they would like to ask a few more questions about this information. The researcher will refer to the risk/safeguarding prompt sheet (see [Appendix 5a](#Appendix5a)) to assist in gathering an appropriate level of information to allow the study supervisors to make a decision about whether this information needs to be passed onto a relevant professional (e.g., their GP, their eating disorder clinician)
3. Ensure the research team have full contact details for the participant or potential participant and arrange a time for a member of the research team to contact them (by telephone) later that day to discuss the information further
4. Contact the study supervisors (RS or SB) by email and/or telephone to seek advice on how to proceed and any actions required
5. Follow any actions agreed with the study supervisors (RS or SB), including (when appropriate) contacting the participant or potential participant at the agreed time to gather further information and/or share planned actions
6. Document the risk/safeguarding information on the ‘Risk Management Log’ within 24 hours and save this on a secure file on the UCL Data Safe Haven. This can then be accessed by the study supervisors, RS and SB

*4.2. Structured contact with a participant to conduct questionnaires, and/or qualitative interviews*

The study researchers will not routinely ask risk questions during structured contacts with a participant (e.g., questionnaires, qualitative interviews). However, there is a chance that the study researchers will become aware of risk/safeguarding information.

The study researchers will have access to support from the study supervisors ([name] and [name], who are both Clinical Psychologists) when making structured contact with families, in the event risk and/or safeguarding information arises, and action needs to be taken. The study researchers will confirm a provisional time with families to conduct structured contacts (e.g., questionnaires, qualitative interviews). Before confirming this appointment time with families, the study researcher will contact the study supervisors (RS or SB) to confirm that at least one of the study supervisors will be available during and after the appointment to respond to any risk/safeguarding information as appropriate. Structured contacts may be scheduled to take place outside of usual working hours (e.g., 9am to 5pm Monday to Friday) as long as a study supervisor (RS or SB) has confirmed that they are available.

Prior to any structured contact with a participant, the study researchers will explain confidentiality and the limits of confidentiality. There should be a common understanding that if the participant shares information that indicates that they or someone else may be unsure or at risk of harm, the study researcher will share this information with the study supervisors (and if necessary, other relevant professionals e.g., their GP, their eating disorder clinician).

In the event that a risk and/or safeguarding concerns arises during structured contacts with participants or potential participants, the study researchers will:

1. Thank the individual for sharing the information and find an early opportunity to explain that this information may need to be shared with the study supervisors and, if necessary, other relevant professionals (e.g., their GP, their eating disorder clinician). Note – an eating disorder clinician will only be contacted if the family remain on the eating disorder service’s caseload during their time within the study (i.e., when on waitlist for assessment/treatment), and if the study supervisors identify that an eating disorder clinician needs to be informed. The eating disorder clinician can then record this information on their electronic patient record system
2. Explain they would like to ask a few more questions about this information. The researcher will refer to the risk/safeguarding prompt sheet (see [Appendix 5a](#Appendix5a)) to assist in gathering an appropriate level of information to allow the study supervisors to make a decision about whether this information needs to be passed onto a relevant professional (e.g., their GP, their eating disorder clinician)
3. Ensure the research team have full contact details for the participant or potential participant and arrange a time for a member of the research team to contact them (by telephone) later that day to discuss the information further
4. Contact the study supervisors (RS or SB) by email and/or telephone to seek advice on how to proceed and any actions required
5. Follow any actions agreed with the study supervisors (RS or SB), including (when appropriate) contacting the participant or potential participant at the agreed time to gather further information and/or share planned actions
6. Document the risk/safeguarding information on the ‘Risk Management Log’ within 24 hours and save this on a secure file on the UCL Data Safe Haven. This can then be accessed by the study supervisors, RS and SB

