## Procedures to be followed by study supervisors when risk issues arise

1. One of the supervisors (who are Clinical Psychologists) will assess the level of clinical risk and make a decision about whether the information gathered is sufficient to make a decision about whether this information needs to be shared or not. In the event that information is not sufficient to make a decision about appropriate action, the study researcher or a supervisor will contact the parent/carer by telephone for further information
2. Where the supervisor assesses the level of risk indicates that this information needs to be shared, the participant will be contacted by telephone (by the study researcher or study supervisor) and advised that this information will be shared with the relevant professional (e.g., their GP, eating disorder clinician). Note – an eating disorder clinician will only be contacted if the family remain on the eating disorder service’s caseload during their time within the study (i.e., when on waitlist for assessment/treatment), and if the study supervisors identify that an eating disorder clinician needs to be informed. The eating disorder clinician can then record this information on their electronic patient record system. If it is not possible to contact the family, the information may need to be shared without their consent
3. If a relevant professional needs to be contacted (e.g., their GP, their eating disorder clinician), it is the responsibility of the study researcher to contact the relevant professionals (with the support of the study supervisors). It will be made clear within these communications that the research team do not hold clinical responsibility for the family so are passing on relevant information to those that do
4. All information surrounding risk and actions taken will be recorded in the ‘Risk Management Log’ within 24 hours and signed off by a study supervisor

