## Risk to self –

Where an individual expresses current and/or past **thoughts and/or actions towards not wanting to be here, suicidal ideation and/or self-harm**, consider gathering the following information:

- Content: What are the thoughts the person is having? Are they having any specific thoughts?
- Duration/intensity: How often do the thoughts happen? How long do the thoughts last? (i.e., fleeting vs. enduring thoughts) How intense are the thoughts? (i.e., from a scale of 0 to 10)
- Triggers: Are there any triggers for the thoughts? Are there any times of the day when the thoughts are more/less likely to happen?
- Intentions: Does the individual have any intentions to act on these thoughts? (i.e., from a scale of 0 to 10)
- Actions: Has the individual taken any actions towards these thoughts? If so, what actions have they taken?
- Management: How does the person manage the thoughts?

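### Appendix 5 handles every risk disclosed in live contact the same way, so a contact can end with only an email sent and imminent danger not yet clinically assessed

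*Protocol*

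**What the plan says.** The Protocol's Risk management section makes Appendix 5 the procedure for the research team throughout the study. Appendix 5 covers three kinds of live contact: unstructured calls (4.1), structured contacts such as telephone questionnaires and interviews (4.2), and guidance sessions (4.4). Each has the same six steps.

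- Step 1: thank the person and explain that the information may be shared.
- Step 2: ask further questions from the prompt sheet in Appendix 5a. For risk to self these include "Does the individual have any intentions to act on these thoughts? (i.e., from a scale of 0 to 10" and "Has the individual taken any actions towards these thoughts? If so, what actions have they taken".
- Step 3: "arrange a time for a member of the research team to contact them (by telephone) later that day to discuss the information further".
- Step 4: contact one of two named supervisors "by email and/or telephone to seek advice on how to proceed and any actions required".
- Step 5: follow the agreed actions, which may include "contacting the participant or potential participant at the agreed time to gather further information and/or share planned actions".
- Step 6: log the information within 24 hours.

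Under the supervisors' procedure for risk issues, a supervising Clinical Psychologist "will assess the level of clinical risk and make a decision about whether the information gathered is sufficient". Supervisor cover is planned. In 4.1, calls are limited to 8am to 8pm on weekdays so that "one of the study supervisors will be available to contact via email and/or their mobile phones if needed". In 4.2 and 4.4, before an appointment is confirmed, the researcher checks that "at least one of the study supervisors will be available during and after the appointment to respond to any risk/safeguarding information".

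**The concern.** Step 2 collects the information that separates a passing thought from an emergency, but steps 3 and 4 do not use it. A young person who reports high intent, or who has already harmed themselves, gets the same call-back and the same choice of channel as one who reports a fleeting thought. Email alone satisfies step 4, and no time is set for sending it or for a reply.

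The person on the call is not the one who assesses clinical risk. Intervention fidelity describes the guide as a postgraduate researcher, and the Optional qualitative interview section allows an Honorary Research Assistant to interview. Assessment belongs to the supervisors. Sections 4.2 and 4.4 also say that risk questions are not asked routinely, so a disclosure there is likely to be unplanned and the researcher will rely on the written list.

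What is at stake is the safety of children and young people with eating disorders. The study's estimates are not affected.

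**Working it through.** The plan gives no figure to reproduce. The check sets the sections side by side and then counts the contacts covered.

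**What each section provides**

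| | 4.1 unstructured | 4.2 structured | 4.4 guidance | 4.3 written |
|---|---|---|---|---|
| Separate route for imminent danger | none | none | none | none |
| Channel to supervisor | email and/or telephone | same | same | same |
| Time limit for reaching supervisor | none | none | none | as soon as possible |
| Follow-up call | later that day | same | same | where appropriate, no time |
| Supervisor cover | weekday hours; email or mobile | confirmed beforehand | confirmed beforehand | not stated |
| Action if no supervisor answers | none | none | none | none |

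Written concerns (4.3) carry an urgency phrase that the three live-contact lists lack.

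**Following the list when the answers are alarming**

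1. The prompt sheet shows high intent or a recent act. No threshold or action is attached to either answer.
2. Step 3 arranges a call-back for later that day.
3. Step 4 can be met by an email. The contact may then be over with no clinician having spoken to the researcher.
4. Step 5 returns to the participant with agreed actions at the arranged time. This implies that a supervisor has replied the same day, but no step says so and none covers the case where no reply has come.

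**Whether another section supplies the missing step**

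- Risk management: further assessment, withdrawal, and informing the GP and other clinicians. No time is stated.
- Novel intervention: immediate reporting to supervisors, but only of possible harmful effects of treatment.
- Supervisors' procedure for risk: information goes to the GP or, if the family is still on the service's caseload, the eating disorder clinician. The one stated fallback is for a family that cannot be reached.
- Supervisors' procedure for safeguarding: adds a safeguarding lead or local team, for safeguarding issues.
- Appendix 5 Introduction and its list of national policies: a general commitment and links, whose content is not in the Protocol.

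**Scheduled contacts covered**

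Inputs are 10 families (Study summary), 8 guidance sessions each (Study design), and 2 feedback appointments and optional interviews (Procedure once participants are enrolled). Assumptions: all 10 families complete treatment, and each family gives at most one young person's and one parent/carer's interview.

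- Guidance sessions: 10 × 8 = 80.
- Feedback appointments: 0 to 10 × 2 = 0 to 20.
- Interviews: 0 to 10 + 10 = 0 to 20.
- Total: 80 + 0 + 0 = 80, up to 80 + 20 + 20 = 120, or 8 to 12 per family.

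The Protocol does not say which subsection governs feedback appointments, but the steps are the same in all three. Telephone questionnaires and 4.1 calls come on top, and their number is not given. No rate of acute disclosure is stated, so the count cannot be turned into expected events.

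**The case against.** The strongest reply is that the arrangement is safer than steps 3 and 4 look in isolation. The call-back is the same day and is meant to convey actions agreed with a Clinical Psychologist, so advice should precede it. Step 5 is where the response is fitted to the risk. Two supervisors are named, one is arranged to be available in each live setting, and contacts outside usual hours in 4.2 and 4.4 need that confirmation. Acute suicidality, recurrent or life-limiting self-harm and high medical or psychiatric risk are exclusions. The screening questionnaires ask about current thoughts of self-harm or suicide, and Risk management bars enrolment where screening finds risk. Parents/carers are encouraged to attend guidance sessions. Potential for participant distress describes interviewers as experienced with families affected by mental health problems and supported by the supervisors.

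All of this stands and lowers the likelihood of harm. None of it provides the missing step. Exclusion works at entry, while Appendix 5 exists for risk that emerges later. Availability is not a requirement to telephone, and it is not a fallback.

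A reader might infer that clinical assessment can be put off indefinitely. The order of steps 3 to 5 does not support that. A reader might also infer that the study has no emergency route at all. The cited national guidance cannot be seen here, so the supportable statement is that no such route is written into the Protocol. Nor does anything bar the researcher from telephoning at once; it is simply not required.

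**Conclusion.** The point holds as a gap in a written safety procedure. In 4.1, 4.2 and 4.4, no answer on the prompt sheet changes the call-back or the channel to the supervisor. A contact may therefore end with only an email sent and imminent danger unassessed by a clinician, and no step covers a supervisor who does not answer. The textual reading is firm. The length of any delay is not known, and same-day supervisor input is implied.

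Exposure is about 80 to 120 scheduled contacts under the assumptions above, with no basis for estimating how many would involve acute risk. The sponsor should make the change because the consequence of failure could be grave and the faster channel is already at hand.

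**What to change.** Add a route for imminent danger to all three lists.

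- **Triggers:** current intent or plan, a recent act of self-harm, immediate danger from others, or doubt. The supervising clinicians confirm the list.
- **Action:** the researcher telephones the available supervisor before the contact ends, does not rely on email or a call-back, and alerts the parent/carer unless the danger comes from them.
- **If there is no answer:** call the second named supervisor, then direct the family to emergency services or call them. This must also apply to contacts held outside usual working hours.
- **Other live disclosures:** keep the order of steps and add to step 4 *as soon as possible, the same day and before the call-back*.

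The cost is a short amendment, some of the supervisors' time to confirm the triggers, and some over-calling of supervisors. The explanation of confidentiality given before 4.2 and 4.4 contacts should also mention that a parent/carer may be told. No extra staff are needed, because supervisor cover is already arranged, both supervisors are already named, and the last step uses emergency services.
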